### Data Collection

#### Outcome Measurement

Outcomes include dissemination performance and message impact across dissemination strategies. The primary outcomes were (1) dissemination reach, measured using platform-level analytics and link-level tracking, and (2) message trust and vaccination intent, assessed through a brief post-viewing survey. Secondary outcomes included engagement metrics (eg, views, watch time, and sharing behaviors) and self-reported changes in views or attitudes toward COVID-19 and influenza vaccination following exposure to the video.

#### Data Collection

Data was collected through three complementary methods to capture both dissemination performance and message impact across strategies:

Survey: a clickable Qualtrics survey link was shared at the end of the video to collect post-intervention data. The brief survey assessed likelihood of flu and COVID-19 vaccination, reactions to the video, how the video was shared, and trust and engagement with the video. Participants who completed the survey were entered into a gift card raffle.Link dissemination tracking: Bitly was used to create individual and personalized links for each dissemination strategy (eg bit.ly/socialmedia). We made a single link for all social media ads, one link per organization for the participating CBOs; and one link per participant for the seeds. We used Bitly analytics to track link engagement, clicks, locations, referrals and type of devices used. All links will corresponded to the same YouTube videos.YouTube analytics: we used YouTube metrics to track platform-level spread and engagement including video reach metrics (impressions, click through rate, views, etc), engagement metrics (watch time, retention, likes, comments, shares), audience insights (age and gender, viewers) and follow-ups (end screen and cards).

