**Figure 1. F1:**
[figure not shown]
Overview of study design and dissemination strategies.

**Table 1. T1:** Study timeline and schedule of activities and assessments.

Study phase	Timeframe	Key activities	Data collected
Formative research	2023‐2025	Cross-sectional survey, egocentric social network analysis, discrete choice experiment, qualitative focus groups, ICAB^a^ consultation	Vaccine attitudes, social media use, network characteristics, message preferences
Intervention development	Jan–Jul 2025	Co-creation of vaccine promotion videos with ICAB, illustration and narration by Indigenous artists and community members, translation into Spanish and Indigenous languages	Not applicable
Dissemination period	Oct 6–Nov 28, 2025	Distribution of identical videos through three dissemination arms (paid social media ads, CBO^b^ distribution, peer-to-peer “seeds”)	Bitly link metrics; YouTube reach and engagement metrics
Post-viewing survey	Oct–Nov 2025	Optional survey linked at end of video	Trust in message, vaccination intent, reactions to video, self-reported sharing
Data consolidation and analysis	Jan 2026–present	Cleaning and integration of Bitly, YouTube, and survey data	Primary and secondary outcome measures
Planned dissemination of results	Spring 2026	Manuscript preparation and submission	Not applicable

a ICAB: Indigenous Community Advisory Board.

b CBO: community-based organizations.

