### Analysis

We will conduct both descriptive and comparative analyses to evaluate the effectiveness of each dissemination strategy. Dissemination patterns within each arm will be summarized, including views, link interactions, and survey responses. Where possible, metrics will be standardized (eg, engagement per view or per dissemination unit) to compare across strategies that could have different scales of deliveries.

Differences between arms will be assessed using aggregated platform (YouTube)- and link-level (Bitly) metrics, as well as survey-based outcomes. For survey measures of trust in the video and vaccination intent, distributions will be compared across dissemination strategies using logistical regressions controlled for sociodemographic characteristics (age, gender, and race/ethnicity). Subgroup analyses (eg, by age group, including adults aged ≥65 y) will be conducted where feasible and will depend on the overall sample size and the distribution of participants within each subgroup.

We will examine indicators of dissemination efficiency, such as reach per dissemination unit (eg, per organization, per seed, or per advertising campaign) and engagement. These comparisons are intended to identify dissemination approaches with greater potential for scalability and sustainability in Indigenous communities. The study is not powered to detect predefined effect sizes. Instead, results will provide empirical benchmarks to guide dissemination strategy selection in larger implementation efforts.

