## Discussion

This study was designed to compare how identical, community-informed vaccine promotion content performs when disseminated through different digital channels among Indigenous communities in California. We hypothesize that dissemination strategies that leverage trusted relationships, such as community-based organizations and peer-to-peer sharing, will demonstrate higher levels of trust and message impact compared to standard social media advertising, while paid ads may achieve greater overall reach.

As public health communication continues to shift into digital spaces, and as people rely on a growing number of virtual platforms to connect, it becomes more important to understand how health messages are shared and how the messenger impacts how people trust those messages. This project responds to a gap in health research by testing three different strategies to distribute the same vaccine information video to Indigenous communities in California, communities that have often been left out of traditional outreach. We compare broad social media ads, which are commonly used today, to more targeted approaches through trusted community organizations and through individual participants sharing within their own networks.

One of the strengths of this study is the combination of digital tracking tools, like Bitly and YouTube, with a post-intervention survey. This allows us to see how messages move across systems and gives us a way to compare which strategy leads to more views, engagement, and trust. These insights can help shape future campaigns by showing how public health information can be distributed in ways that are more meaningful and relevant for the people they aim to reach. In addition, we ensure accessibility of the message by making it available in four Indigenous languages spoken in California.

We do expect some limitations. For example, the success of the seed-sharing strategy depends on whether participants decide to share the video, and whether the people they share it with choose to watch it and respond to the survey. These steps are voluntary, and it is anticipated that there may be some participant drop-off.

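### Trust and vaccination intent are compared only among viewers who finish the video and choose to answer, so the ranking of strategies can be biased, in a direction and by an amount the documents do not fix

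*Protocol article*

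**What the plan says.** All references are to the protocol article.

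- **Outcome status.** Outcome Measurement lists two primary outcomes. The second is "message trust and vaccination intent, assessed through a brief post-viewing survey".
- **Where the survey sits.** Under Data Collection, "a clickable Qualtrics survey link was shared at the end of the video to collect post-intervention data". Table 1 describes it as "Optional survey linked at end of video".
- **Comparison.** Under Analysis, for trust and intent, "distributions will be compared across dissemination strategies using logistical regressions controlled for sociodemographic characteristics (age, gender, and race/ethnicity").
- **Standardisation.** The same section says "Where possible, metrics will be standardized (eg, engagement per view or per dissemination unit"). Trust and intent are not named there. Views, link interactions and survey responses are to be summarised within each arm.
- **Tracking by arm.** Under Data Collection, "We made a single link for all social media ads, one link per organization for the participating CBOs; and one link per participant for the" (the sentence ends with the third arm, the seeds). All links lead to the same YouTube videos, and no retention figure by arm is described.
- **Drop-off.** The Discussion gives the seed strategy as an example of a limitation, noting that recipients may not watch or answer: "These steps are voluntary, and it is anticipated that there may be some participant drop-off". It describes no analysis in response.

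**The concern.** To enter the trust and intent comparison, a person must click, stay to the end and then decide to answer. The last two steps happen after exposure. Someone sent the video by a friend or by their own organisation may stay and answer for different reasons from someone who met it as an advertisement. The comparison therefore conditions on an event that the strategy itself may influence.

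Age, gender and race/ethnicity do not repair this. Within any stratum of these covariates, people who trust the message may still be more, or less, likely to finish and answer than people who do not.

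The Discussion hypothesises that community organisations and peers will do better than ads on trust and impact, while ads may reach more people. The Analysis section says the results should inform which strategies to choose in larger programmes. Selection into the survey could hide, exaggerate or invert that trust contrast.

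**Working it through.** The article states no response rate, retention rate, trust level or sample size, so there is no figure to reproduce. The check is algebraic, and **every rate below is assumed**.

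**Notation, for each arm**
- π: share of all clickers who would report trust if asked.
- rT, rN: probability that a trusting or a non-trusting clicker finishes and answers.

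**Formulas**
- Trust among respondents = π·rT / [π·rT + (1−π)·rN].
- Odds of trust among respondents = [π/(1−π)] × (rT/rN).
- Observed odds ratio = true odds ratio × [(rT/rN) in arm A ÷ (rT/rN) in arm B].

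So the overall response rate does not matter by itself. What matters is whether rT/rN differs between arms. The same relation holds within each covariate stratum, and for intent in place of trust.

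**Assumed truth.** Community arm π = 60%, ads arm π = 50%. True odds ratio = (0.6/0.4)/(0.5/0.5) = 1.5. The order reverses when rT/rN in the ads arm exceeds 1.5 times that in the community arm.

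| Community rT/rN | Ads rT/rN | Trust among respondents, community vs ads | Observed odds ratio |
|---|---|---|---|
| 30%/30% | 10%/10% | 60.0% vs 50.0% | 1.5 × 1/1 = 1.5 (unbiased) |
| 40%/20% | 10%/5% | 75.0% vs 66.7% | 1.5 × 2/2 = 1.5 (unbiased) |
| 30%/30% | 10%/5% | 60.0% vs 66.7% | 1.5 × 1/2 = 0.75 (reversed) |
| 30%/20% | 10%/3% | 69.2% vs 76.9% | 1.5 × 1.5/3.33 = 0.675 (reversed) |
| 30%/30% | 5%/10% | 60.0% vs 33.3% | 1.5 × 1/0.5 = 3.0 (exaggerated) |

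Third row in full. Community: 0.6×0.30 = 0.18 and 0.4×0.30 = 0.12, so 0.18/0.30 = 60.0%. Ads: 0.5×0.10 = 0.050 and 0.5×0.05 = 0.025, so 0.050/0.075 = 66.7%.

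**Second check.** A latent-normal simulation (2 million draws) kept 25% of the community audience and 5% of the ads audience, with correlation ρ between staying and trust.
- ρ = 0: 60% vs 50%, no bias.
- ρ = 0.3: 74.4% vs 74.0%, difference erased.
- ρ = 0.5: 83.9% vs 87.7%, reversed.
- ρ = −0.3: 44.7% vs 26.0%, the arm with more loss is penalised.

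**Bounds for all clickers.** With response r and observed trust p, the worst case is p·r and the best case is p·r + (1−r). For p = 60%:
- r = 5%: 3% to 98%
- r = 10%: 6% to 96%
- r = 30%: 18% to 88%

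**Per-click yield.** Trusting respondents per click = π·rT. In the third row this is 18 per 100 clicks (community) and 5 per 100 (ads). The yield ranks the arms as the assumed truth does, but its ratio is 18/5 = 3.6 where the ratio of true trust is 60/50 = 1.2. The excess is response propensity: rT is 30% against 10%, and 1.2 × 3 = 3.6.

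**The case against.** **Greater loss alone does not bias the result.** A reader might infer that the planned comparison automatically favours whichever arm loses most of its audience, or that ads will look good because sceptics leave first. The documents support neither. In the second row of the table, response is 32% in the community arm and 7.5% in the ads arm, yet the odds ratio stays at 1.5. The video lasts 30 seconds, and a raffle of forty US $100 gift cards gives a reason to answer that need not relate to trust. This objection stands: what is shown is that bias is possible, not that it has a known direction.

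**Part of the reporting is already planned.** The Abstract counts survey completion as engagement, and the Analysis section standardises engagement per view or per unit where possible. Completions relative to audience can fairly be read as covered. That stands too, but it does not tie trust or intent to a denominator. Views are also a weak denominator by arm, because all links share the same videos; Bitly clicks are the count that the article separates by arm.

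**A per-click yield could mislead in its turn.** A reader might conclude that strategies should be ranked on trusting respondents per click. They should not: as the factor of 3.6 against 1.2 shows, that figure scores willingness to answer as message impact, and it could favour the arms already hypothesised to win.

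**The study is a benchmark exercise.** It is not powered for set effect sizes, no rule ranks strategies on trust alone, and sensitivity analyses are often left to an analysis plan, which is not shown. This lowers the stakes. It does not remove the point, because the article itself fixes the instrument, its placement, the primary status of the outcome and the comparison.

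**Conclusion.** The concern holds in a limited form. A primary outcome is observed only in self-selected respondents at the end of the video, and the stated covariates cannot be relied on to remove selection on trust or intent. Followed as written, the comparison can misrank the strategies.

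This requires that response be related to trust or intent and that the relation differ between arms. With assumed true trust of 60% and 50%, the order reverses once rT/rN in the ads arm is more than 1.5 times that in the community arm. The opposite pattern exaggerates the hypothesised difference. Without response rates, neither the size nor the sign of any bias can be stated, and at 5% to 30% response, worst- and best-case bounds are too wide to settle it.

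**What to change.** In the Analysis section, keep the adjusted regression and add the following.

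1. For each arm, report Bitly clicks, survey completions per click, and respondents reporting trust and reporting intent per 100 clicks.
2. Give worst- and best-case bounds for non-respondents, or a sensitivity analysis that varies rT/rN between arms and shows the ratio at which the ranking changes.
3. State that the regression applies to people who finished the video and responded.
4. Draw no ranking of strategies on message impact from the respondent-only result alone. The per-click yield supplements that result and does not replace it.

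**Cost.** A small amount of analysis and wording. Dissemination ended on November 28, 2025, so the survey's placement cannot change, but clicks by link and survey answers are already collected. Assigning survey answers to arms is needed for the planned regression in any case.

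**Downside.** The yield mixes response propensity with trust and counts every non-respondent as not reporting trust. Repeat clicks inflate its denominator, and viewers who arrive without a Bitly click can enter its numerator only. These limits should be stated beside the figures.

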### Study Design and Dissemination Arms

In our trial, we will test 3 dissemination strategies for our intervention. The videos will be hosted on our university’s institutional YouTube channel, with separate versions in each focal language. Videos will be distributed through the following three dissemination approaches for one month:

Paid social media ads: videos will be shared through a paid ad campaign through Facebook and Instagram. They will be shared as posts with a link to the YouTube video. The audience will be targeted using geolocation through zip codes with high Indigenous populations in California (based on ICAB and census data), language including Spanish, and interests identified with our ICAB.Community based organizations (CBOs): ICAB-affiliated CBOs will share the links to the videos using their usual communication channels used with their members (eg, WhatsApp, social media, email lists, CBO websites).Individual seeds: We will recruit Indigenous-identifying participants from our previous survey (listed above) who consented to future contact. Each individual will receive a link and be asked to share the video with five or more contacts in their network using their preferred method (eg, SMS, WhatsApp, social media).

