## Results

The study was funded in January 2023. Intervention development, including formative work and the co-creation and translation of vaccine promotion videos, was completed in July 2025. Dissemination activities and participant-facing data collection across all three study arms were conducted between October 6 and November 28, 2025, aligned with the COVID-19 and influenza vaccination season in the United States (Table 1).

Three dissemination strategies were implemented during this period. For the community-based organization arm, five community-based organizations participated in distributing the video links to their members using established communication channels. For the peer-to-peer dissemination arm, 68 Indigenous-identifying participants from prior research were recruited as individual “seeds” and provided with personalized links to share the videos within their social networks. In parallel, targeted paid social media campaigns were conducted on Facebook and Instagram using geolocation, language, and interest-based targeting strategies informed by formative research and guidance from the ICAB.

All dissemination activities concluded on November 28, 2025. Data from Bitly link tracking, YouTube analytics, and follow-up surveys were consolidated and prepared for analysis beginning in January 2026. Outcome analyses are underway, and primary results are expected to be submitted for publication in Spring 2026.

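### All three arms' links lead to the same YouTube videos, so YouTube views and engagement have no arm-specific value, yet the plan compares arms on them

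*Protocol article*

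**What the plan says.** Under Data Collection, the protocol article describes how arm identity is tracked: "a single link for all social media ads, one link per organization for the participating CBOs; and one link per participant for the seeds". The same paragraph then says "All links will corresponded to the same YouTube videos". Under Study Design and Dissemination Arms, the videos are hosted on one institutional YouTube channel "with separate versions in each focal language". Intervention Development and Design adds two visual adaptations, one for each community group. Ethical Considerations says that the platforms supplied aggregate metrics only.

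Under Outcome Measurement, the first primary outcome is "dissemination reach, measured using platform-level analytics and link-level tracking". Views and watch time appear among the secondary engagement outcomes. The Analysis section states: "Differences between arms will be assessed using aggregated platform (YouTube)- and link-level (Bitly) metrics, as well as survey-based outcomes". It also plans to summarize views within each arm and to standardize engagement by views. The Discussion presents the combined tools as a way to see which strategy produces more views, engagement and trust.

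For the survey, Data Collection says "a clickable Qualtrics survey link was shared at the end of the video to collect post-intervention data". One listed survey topic concerns sharing of the video, and Table 1 lists it as self-reported sharing. Trust and vaccination intent, the second primary outcome, are to be compared between strategies by logistic regression.

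**The concern.** Arm identity is carried by the Bitly link and, as described, goes no further than the click. After the click, viewers from the ads, the community-based organizations (CBOs) and the seeds arrive at the same videos, together with anyone who finds them another way. An aggregate count taken at the video cannot then be divided by arm.

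The study exists to compare strategies. Its hypothesis is that paid ads reach more people while the CBO and seed routes earn more trust and impact. If part of the reach outcome and all YouTube engagement have no value by arm, the results paper must either leave those comparisons out or fill them with an unstated allocation rule. The abstract also offers the method as a model that others can replicate, so the gap would be copied.

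**Working it through.** The article states no sample size, power or effect size, so there is no figure of its own to reproduce. The check follows the data from link to video to survey.

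**Inputs**
- Links: one for ads, one per CBO, one per seed (Data Collection).
- Units (Results): "five community-based organizations participated in distributing the video links" and "68 Indigenous-identifying participants from prior research were recruited".
- Destination: the same videos for all links (Data Collection).
- Split of hosted videos: language, plus the community adaptation; no split by arm.
- Platform data: aggregate (Ethical Considerations).

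**Step 1: number of links.** With one link per unit, 1 + 5 + 68 = 74 links feed the same set of videos.

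**Step 2: what can be split by arm.**

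| Measure | Where recorded | Value by arm as described? |
|---|---|---|
| Clicks, with location, referral and device | Bitly link | Yes, also per CBO and per seed |
| Views, watch time, retention, likes, shares | YouTube video | No, pooled |
| Engagement per view | YouTube video | No, the arm-specific denominator is missing |
| Trust, vaccination intent | Survey at end of video | Only if some identifier or self-report is used |

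**Step 3: can clicks be used to divide the views?** For one video, let V be its views, c the clicks by arm, r the views per click by arm, and o the views that came through no tracked link. Then

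V = c(ads)·r(ads) + c(CBO)·r(CBO) + c(seed)·r(seed) + o.

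V and the three c are observable at best. The three r and o are unknown: one equation, four unknowns. Dividing V in proportion to clicks assumes equal r in all arms. Views by arm would then only restate clicks, and a difference in what happens after the click would be assumed away.

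**Step 4: can traffic source or date separate the arms?** Traffic source cannot do so reliably. The ads run on Facebook and Instagram, CBOs may use social media and WhatsApp, and seeds may use the same channels. Date does not help either, since all three arms ran between October 6 and November 28, 2025.

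**Step 5: survey, if arm was taken from self-report (illustration).** Assume three arms of equal size, with a share m of each arm's respondents misassigned evenly to the other two. The observed proportion in arm i is

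p′(i) = (1 − m)·p(i) + (m/2)·[p(j) + p(k)].

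Subtracting the same expression for arm j gives

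p′(i) − p′(j) = (1 − m − m/2)·[p(i) − p(j)] = (1 − 1.5m)·[p(i) − p(j)].

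| m (assumed) | Share of true difference left |
|---|---|
| 10% | 1 − 0.15 = 85% |
| 20% | 1 − 0.30 = 70% |
| 30% | 1 − 0.45 = 55% |
| 2/3 (random labels) | 1 − 1 = 0% |

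Nothing in the article gives m. The table shows how sensitive the comparison would be, not how much error is present.

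**The case against.** The strongest reply has four parts.

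**The survey.** A reader might infer that survey answers cannot be assigned to an arm at all. The article does not support that. It describes no arm code in the survey link, but it is a condensed account, and the full protocol or the SAP may hold one. It also lists a survey topic on sharing, which could classify respondents by their own report. That route is weak: the topic may mean onward sharing rather than how the video arrived, channels overlap between arms, and videos can be forwarded across arms. Weak is not the same as impossible, so for the survey the request is only to say how arm was derived.

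**Other attributable data.** Bitly gives locations, referrals and devices as well as clicks, and reach per organization, seed or campaign can be computed from the links. This stands, and the link-level part of the reach outcome is unaffected. Facebook and Instagram analytics are also named as aggregate sources. They could describe the ad campaign, but the article describes no matching data for the other two arms.

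**The hedge on feasibility.** The Analysis section standardizes metrics only where this can be done. That qualifier applies to standardization. The sentence committing to between-arm comparison on YouTube metrics carries no such condition.

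**A study of benchmarks.** The article says that the study is not powered for set effect sizes. This lowers the weight of any single test, but a benchmark for a strategy still needs a value for that strategy.

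The YouTube point survives all four. It rests on two statements in the text that do not fit together, not on something left out.

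**Conclusion.** The point holds for YouTube metrics. As described, every YouTube-based contrast between arms lacks arm-specific data: the platform part of the first primary outcome, the YouTube-based secondary engagement outcomes, the within-arm summary of views, and engagement per view. This rests on the plain reading that the arms share the same uploads and that the data are aggregate. Bitly link metrics remain valid for comparing arms.

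For the survey, the conclusion is narrower: the method of assigning respondents to arms is not described, and the only visible candidate is an ambiguous self-report. If self-report was used, a difference between arms would shrink to 85%, 70% or 55% of its true size at 10%, 20% or 30% misassignment, assuming equal arms and even misassignment.

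It would go too far to say that the trial cannot compare its strategies. It can do so on clicks, and on trust and intent to the extent that arm assignment can be defended.

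**What to change.** **YouTube and reach**
1. Base between-arm reach and efficiency on link-level Bitly metrics: clicks per arm, per organization, per seed and per campaign.
2. Report YouTube views, watch time, retention, likes and shares pooled per video.
3. Remove YouTube metrics from the between-arm comparison, the within-arm view summaries and the per-view standardization in Analysis. Remove the platform-level part of the first primary outcome as an arm contrast, and the Discussion's claim about views and engagement by strategy.

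**Survey**
4. State how each respondent's arm was derived. If by self-report, say so, give the item wording, and keep multiple or unsure sources as a separate category.
5. In that case, add a three-arm misclassification sensitivity analysis, for example over 10% to 30%.

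**Cost.** Steps 1 to 4 are rewording and reporting, and step 5 is one added analysis. The article says that outcome analyses were still under way, so the changes can be made before the results paper. The price is that the YouTube arm comparisons are given up.

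**For a repeat only.** Separate uploads per arm, with a coded survey link on each, would carry arm identity past the click. They cannot help this trial, since dissemination has ended. They also have a cost: more videos to manage, view counts split over more uploads, and no protection against forwarding across arms.
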